## Method/design

### Aims

The overall aim of *Swiss Preschoolers’ Health Study (SPLASHY)* is to investigate how stress (as a paradigm for a potentially health challenging predictor) and PA (as a paradigm for a potentially health promoting predictor) influence children’s psychological and physiological health by focusing on four essential health outcomes, i.e. cognitive functioning, psychological well-being, adiposity and motor skills. The main hypotheses for the respective research questions are the following:Chronic exposure to environmental stressors (major life events, chronic day-to-day stressors), chronic physiological stress responses (dysregulations of the hypothalamic-pituitary-adrenal (HPA) axis, dysregulation of the autonomic nervous system (ANS), and the dysregulation of acute laboratory induced stress reactivity to a standardized stressor) are associated with/predict increased current and prospective adiposity, reduced cognitive functioning, and reduced psychological health (i.e., emotional problems, behavioral problems and dysfunctional eating behavior scores).High levels of total physical activity and more time spent in moderate-to-vigorous physical activity correlate with/predict current and prospective lower levels of adiposity, better cognitive functioning and motor skill performance and increased psychological health.Stress exposure and physical activity have an impact on psychological and physiological stress responses.Aspects of child’s development and health (cognitive and emotional development, self-regulation skills, adiposity, motor skills) are related to each other.The strength of all these associations vary with age.Environmental characteristics such as *sociocultural environment* (German vs French part of Switzerland), *child care center characteristics* (quality, health promoting activities), *parental characteristics* (family atmosphere, parenting style, parenting stress and family lifestyle, parental BMI, socioeconomic status), *psychological child characteristics* (temperament, emotion and self regulation, pre- and postnatal conditions*),* and *physiological child characteristics* (lifestyle behavior, adiposity) impact on the above mentioned outcomes and have a moderating role in the relationship between stress, PA and psychological and physiological health of preschool children. It is further assumed that the strength of association varies with age and that children’s characteristics (lifestyle, temperament, emotional well being and self regulation) and environmental characteristics (family atmosphere, parental style, socioeconomic status, child care center characteristics and the sociocultural environment such as German-French speaking parts of Switzerland) may moderate the relationship of stress and physical activity on psychological and physiological health outcomes.

### Design

SPLASHY is a prospective cohort study including children during early childhood within two sociocultural areas of Switzerland (German and French speaking part). The project uses a multi-site approach including four research groups recruiting child care centers within five cantons of Switzerland (Aargau, Bern, Fribourg, Vaud, Zurich) which together made up 50 % of the Swiss population in 2013.

### Study sample

Sample size calculations were based on the data simulation software MLPowSim 2 in combination with R, version 2.13.1, with 5000 permutations per simulation. We thereby selected an effect size *r* = 0.18 which was the minimum expected effect size in any sub-project in order to have a sufficiently high sample size to test hypotheses in any sub-project. Further conditions were: statistical power 1–β = 0.8, α = 0.05, two-sided test.

Thus, the minimal sample size to have sufficient power at the third assessment wave was calculated to be 240 children. For reasons of feasibility, we planned to recruit 96 child care centers (24 for each of the four research groups). Based on a previous study [100] we presumed that around 12 children per child care center or 1150 children in total would be present and could be invited on a given afternoon of testing. We assumed a participation rate of 40 % or 500 children at T1 with 5.2 children per child care center. In addition, we assumed a worst case scenario in which the analysis was based on data from the third assessment wave (T3, not part of the current study design), where an additional 48 % of the data was expected to be missing. This estimated dropout rate of 48 % was based on a dropout rate of 20 % between T1 and T2 and another 40 % dropout between T2 and T3 resulting in a final sample size at T3 of 240 children. The higher dropout of 40 % between T2 and T3 is based on the situation that merely all children will have left the child care center by this time and will go to kindergarten elsewhere.

Child care centers were recruited in five cantons Aargau (AG), Berne (BE), Fribourg (FR), Vaud (VD), Zurich (ZH) which together contained 50 % of the Swiss population in 2012 [101]. The selection procedure was stratified according to one stratum with four levels: urban community and rural community with high SES (above-average) and low SES (below-average) each based on the prevalence of child care centers in the respective communities. For FR and BE, all child care centers were invited to participate due to a low number of existing child care centers in these cantons.

Urban communities were defined as the biggest cities of each canton as well as cities >100’000 inhabitants. This included Zurich and Winterthur (ZH), Bern (BE), Fribourg (FR), Aarau (AG), Lausanne (VD). All other communities were defined as rural communities.

Socioeconomic status was defined by the maternal education level of the community based on the report of the 2010 SNF ‘NFP 60 “familienergänzende Kinderbetreuung und Gleichstellung” (REF [102]). Thus, child care centers for which the community’s proportion of mothers with a university degree was higher or lower than the median were accordingly defined to have high or low SES, respectively.

For the larger urban communities, a different method for SES stratification was chosen as the community SES would not represent it appropriately. The list of child care centers was divided into high and low SES using the definition of SES according to the Swiss neighbourhood index of socioeconomic status [103]. Thereby, deciles of the index were constructed and high SES was defined as the deciles 6–10 and low SES as the deciles 0–5.

A total number of 639 child care centers in the French and German part of Switzerland were contacted in the period between January 2013 and October 2014 by four different research groups and were informed on study participation (see Fig. 2). Of these, 126 child care centers agreed to participate and to inform the parents. Reasons for refusals were lack of time (26 %), too few (less than 4) children of the selected age group present in child care on a given afternoon (21 %), no interest (21 %) and organizational changes (13 %). Further, 42 centers had to be excluded after the preparation of testing dates due to too few (less than 2) participating children (78 %) or for other reasons (12 %). The final sample consisted of 84 child care centers that participated, which is 12 % less than the originally planned number of 96 child care centers.

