**Fig. 2 Fig2:**
[figure not shown]
Recruitment and participants flow

In addition, instead of the expected number of 12 children per child care center, a mean of 7.6 children (2–6 years old) were present at a given assessment afternoon and were invited to participate. The participation rate for these was, however, much higher than expected (73.9 %, *n* = 476 at T1). In summary, expected and real recruitment numbers differed by 24 children in the total sample. Therefore, for T2, new arriving children of the same child care centers are currently still recruited in order to obtain the desired number of children at T2 and T3. Note that the number of 240 children at T3 leads to slightly increased power when coming from 84 rather than 96 child care centers because of the reduced design effect. However, this beneficial effect is expected to be very small.

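### Two planning figures in the sample-size paragraph are wrong as written: 40 % of 1150 is 460, not 500, and losing 20 % then 40 % is 52 % dropout, not 48 %; the 240 at T3 still follows from 500

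*Protocol article*

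**What the plan says.** All planning figures are in the Study sample section of the protocol article.

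- **Target.** The effect size is set by "We thereby selected an effect size *r* = 0.18 which was the minimum expected effect size in any sub-project", under the conditions "statistical power 1–β = 0.8, α = 0.05, two-sided test". From a multilevel simulation, "the minimal sample size to have sufficient power at the third assessment wave was calculated to be 240 children".
- **Invitations.** For feasibility, "we planned to recruit 96 child care centers (24 for each of the four research groups"), and the authors presumed that around "12 children per child care center or 1150 children in total would be present" on a testing afternoon.
- **Participation.** "We assumed a participation rate of 40 % or 500 children at T1 with 5.2 children per child care center".
- **Attrition.** 48 % of the data is expected to be missing by T3. "This estimated dropout rate of 48 % was based on a dropout rate of 20 % between T1 and T2", followed by a further 40 % between T2 and T3, which ends at 240 children.
- **Outcome of recruitment.** After Fig. 2, the article reports 476 children at T1 and a participation rate of 73.9 %. It says that "expected and real recruitment numbers differed by 24 children in the total sample", and that new children at the same centers are therefore being recruited at T2.

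**The concern.** Two steps in the chain from invitations to T3 do not agree with their own inputs. A participation rate and a head count are given as equivalent although they differ by 40 children. A share retained is reported as a share lost.

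The second slip has the more practical effect. The minimum of 240 is met exactly in the plan, with no reserve, and T1 recruitment ended below 500. Whether the 476 T1 children appear sufficient for T3 depends on whether the expected loss is 48 % or 52 %. A reader who takes the printed dropout figure at face value gets the wrong answer.

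The first slip affects the recruitment benchmark. Against 500, the realised 476 is 24 short. Against 40 % of 1150, it is 16 over.

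**Working it through.** **Inputs (all from Study sample).** 96 centers; about 12 children each, 1150 in total; 40 % participation; 500 at T1; 5.2 per center; dropout 20 % then 40 %; cumulative dropout printed as 48 %; 240 required and expected at T3; r = 0.18, 80 % power, two-sided α = 0.05; 476 realised at T1.

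**1. The article's own 240**

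- As a required number: the Fisher-z formula n = ((1.960 + 0.842) / atanh(0.18))² + 3 gives 240.0. This ignores clustering. The article used simulation and prints no intraclass correlation, so the match is a check on size and does not reconstruct the method.
- As an expected number: 500 × (1 − 0.20) × (1 − 0.40) = 500 × 0.48 = 240. It reproduces exactly.

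**2. Participation**

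- 96 × 12 = 1152, consistent with the printed 1150.
- 0.40 × 1150 = 460, and 460 / 96 = 4.8 per center.
- 500 / 1150 = 43.5 %; 500 / 96 = 5.2 per center; 5.2 / 12 = 43.3 %.

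So 500 and 5.2 agree with each other, and 40 % agrees with neither.

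**3. Dropout**

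- Retained: 0.80 × 0.60 = 0.48. Lost: 1 − 0.48 = 0.52.
- A true 48 % loss from 500 would leave 500 × 0.52 = 260, not 240.

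**4. What each combination gives at T3**

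| T1 number | Loss applied | T3 number | Power for r = 0.18 (Fisher z, unclustered) |
|---|---|---|---|
| 500 (stated) | 52 % (stage rates) | 240 | 80.0 % |
| 500 (stated) | 48 % (printed) | 260 | 83.1 % |
| 460 (40 % of 1150) | 52 % (stage rates) | 221 | 76.6 % |
| 460 (40 % of 1150) | 48 % (printed) | 239 | about 80 % |

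**5. The realised T1 sample**

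- At the printed 48 % loss: 476 × 0.52 = 247.5, about 248, above 240.
- At the 52 % loss implied by the stage rates: 476 × 0.48 = 228.5, about 228, below 240; power about 78 %.
- Largest loss that still leaves 240: 1 − 240 / 476 = 49.6 %, which lies between the two figures.
- Size of the gap at T2: 240 at T3 needs 240 / 0.60 = 400 at T2, and the T1 children supply 476 × 0.80 = 381. About 20 new children at T2 would close it, on the assumption that they are lost at the same 40 % rate as the others. They would contribute data from T2 onward only.

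**The case against.** A reader might infer that the stated inputs yield 221 children at T3, so that the plan was underpowered from the start. The article does not support that. The 500 at T1 is itself a stated input. It is backed by 5.2 per center and by the later count of a 24-child shortfall (500 − 476), and with the two stage dropouts it gives 240 exactly. The 221 needs the 40 % to override both. The reading with the fewest changes is that 40 % should be about 43 % and that 48 % carries the wrong label; neither correction moves 240.

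A reader might also take 228 as the expected T3 sample. That treats the cohort as closed, whereas the article says new children are recruited at T2 to reach the desired numbers at T2 and T3. The 228 is a projection for the T1 children alone.

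A third inference, that retention would be monitored against a wrong threshold, has no basis: no monitoring rule tied to 48 % appears in the article.

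The consequence is limited as well. The article presents T3 as a worst case outside the present design. On the same unclustered approximation, 476 children at T1 give about 98 % power for r = 0.18, and 381 at T2 about 94 %. All these power figures ignore clustering and should be read as approximate.

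These points stand and set the severity. They leave two printed figures that are wrong and, for the dropout, a printed value that reverses the apparent adequacy of the T1 sample.

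**Conclusion.** The point holds as a minor correction. The participation rate and the T1 number disagree by 40 children (460 against 500). Cumulative dropout is understated by 4 percentage points, because the retained share is printed as the lost share.

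The required 240 is unchanged, and the expected 240 follows from 500 with the stage dropouts. A T3 number of about 221, with about 77 % power, applies only if 40 % participation was the real planning assumption; the article does not settle this, though its other figures favour 500. From the realised 476, the stage rates leave about 228 of the T1 children (about 78 % power), which is below the minimum until the T2 top-up is counted. The size of that top-up is not given in the article. The arithmetic on counts rests only on printed figures; the power values rest on the unclustered Fisher-z approximation.

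**What to change.** 1. State cumulative dropout by T3 as 52 %, with 48 % retained.
2. State participation as about 43 %, to match 500 children and 5.2 per center. If 40 % was the true assumption, state 460 at T1, 4.8 per center and about 221 at T3 instead, and change the reported shortfall of 24 to a surplus of 16.
3. Where T3 is projected from the realised sample, give about 228 from the 476 T1 children and show separately the number recruited at T2 and its expected contribution toward 240.

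The cost is a few corrected figures and one added sentence. The correction itself calls for no change to the design, the required number or the analysis, and for no children beyond the top-up already under way.

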**Fig. 2 Fig2:**
[figure not shown]
Recruitment and participants flow

In addition, instead of the expected number of 12 children per child care center, a mean of 7.6 children (2–6 years old) were present at a given assessment afternoon and were invited to participate. The participation rate for these was, however, much higher than expected (73.9 %, *n* = 476 at T1). In summary, expected and real recruitment numbers differed by 24 children in the total sample. Therefore, for T2, new arriving children of the same child care centers are currently still recruited in order to obtain the desired number of children at T2 and T3. Note that the number of 240 children at T3 leads to slightly increased power when coming from 84 rather than 96 child care centers because of the reduced design effect. However, this beneficial effect is expected to be very small.

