### Statistical analysis

The main analyses will be carried out according to the study analysis plan. First, descriptive statistics will be used for child care centers’ and children’s characteristics. Analyses will be adjusted for participants’ differences and/or cluster baseline characteristics i.e. age, gender and for further covariates such as SES depending on the respective research question. Multilevel models will be used to analyse the main outcomes of the study with child care center as upper and child as lower hierarchical level. For certain analyses, missing values are dealt with using either multiple imputation or maximum likelihood procedures which have repeatedly shown to provide unbiased parameter estimates under the missing at random (MAR) condition [135]. Internal validation will be used for assessing the self-developed Picture Stress Test. Further, longitudinal data will be analysed using multilevel models with child as upper and time within child as lower hierarchical level. This model can be extended by including child care center as an additional uppermost level if appropriate.

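### With 240 children fixed at T3, moving from 96 to 84 centres raises the design effect rather than reducing it, so the stated power gain does not hold in general (minor)

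*Protocol article*

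**What the plan says.** The Study sample section sets the target for an expected correlation of r = 0.18, "which was the minimum expected effect size in any sub-project", with "statistical power 1–β = 0.8, α = 0.05, two-sided test". It names multilevel simulation software: "Sample size calculations were based on the data simulation software MLPowSim 2 in combination with R, version 2.13.1, with 5000 permutations per simulation". The result is that "the minimal sample size to have sufficient power at the third assessment wave was calculated to be 240 children". The plan was 96 centres and 500 children at T1 (5.2 per centre). Dropout of 20 % and then 40 % leaves 240 at T3, a wave that the article calls a worst case and places outside the current design.

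Recruitment fell short on centres: "The final sample consisted of 84 child care centers that participated". With 476 children at T1, the article says that newly arriving children in the same centres are being recruited. It then adds the remark at issue, that 240 children at T3 would have "slightly increased power when coming from 84 rather than 96 child care centers because of the reduced design effect", and expects this benefit to be very small.

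The Statistical analysis section states: "Multilevel models will be used to analyse the main outcomes of the study with child care center as upper and child as lower" level. The last hypothesis under Aims includes centre characteristics and the German- or French-speaking region as predictors and moderators.

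**The concern.** The remark compares two designs with the same number of children and different numbers of centres. Fewer centres then means more children in each, and for a positive within-centre correlation larger clusters carry a larger design effect. The article says the opposite and does not limit the statement to particular predictors.

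What is at stake is a stated power property. A reader is told that having fewer centres helped power slightly. For the hypotheses on centre characteristics and language region, where the number of centres matters most, the direction is reversed. Because the design effect is mentioned, a reader may also take it that 240 includes a margin for clustering in those hypotheses, and no such margin is visible.

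**Working it through.** **Inputs from the Study sample section.** r = 0.18; power 0.80; two-sided α = 0.05; 240 children at T3; 96 centres planned, 84 obtained; 500 children planned and 476 obtained at T1; dropout 20 % from T1 to T2. **Assumption:** the within-centre ICC of the outcome is not given, so a range of 0.01 to 0.20 is shown.

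**Step 1: the article's own figure.** For independent children, by Fisher's z:

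n = ((1.95996 + 0.84162) / atanh(0.18))² + 3 = (2.80158 / 0.18198)² + 3 = 239.9995, that is 240.

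This equals the stated size, so 240 corresponds to a design effect of 1. Other unclustered formulas come close: about 237 with a noncentral t test of the slope, and 235 with a Wald test.

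**Step 2: cluster size.** At T3, 240/96 = 2.50 and 240/84 = 2.86. At T1, 500/96 = 5.2 planned and 476/84 = 5.67 obtained. Both comparisons go up. Fewer children were present per centre than expected (7.6 against 12), but participation was higher, so participants per centre did not fall.

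**Step 3: design effect and power for a centre-level predictor.** DE = 1 + (m − 1) × ICC; effective n = 240/DE; power = Φ(atanh(0.18) × √(effective n − 3) − 1.96).

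| Assumed ICC | DE, 96 centres | DE, 84 centres | Effective n | Power, 96 | Power, 84 |
|---|---|---|---|---|---|
| 0.01 | 1.015 | 1.019 | 237 to 236 | 79.4 % | 79.3 % |
| 0.05 | 1.075 | 1.093 | 223 to 220 | 77.1 % | 76.4 % |
| 0.10 | 1.150 | 1.186 | 209 to 202 | 74.2 % | 72.9 % |
| 0.20 | 1.300 | 1.371 | 185 to 175 | 68.9 % | 66.5 % |

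The sign does not depend on the ICC, only the size does.

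**Step 4: predictors measured on the child.** In a random-intercept model with outcome ICC ρy and predictor ICC ρx, the variance of the slope relative to independent data is

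(1 − ρy)(1 + (m − 1)ρy) / (1 + (m − 2)ρy − (m − 1)ρyρx).

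| ρy | ρx | Factor, 96 to 84 | Power, 96 to 84 |
|---|---|---|---|
| 0.05 | 0 | 0.9963 to 0.9955 | 80.15 % to 80.18 % |
| 0.05 | 0.05 | 1 to 1 | 80.0 % to 80.0 % |
| 0.05 | 0.20 | 1.0111 to 1.0136 | 79.6 % to 79.5 % |
| 0.10 | 0 | 0.9857 to 0.9829 | 80.57 % to 80.68 % |
| 0.10 | 0.10 | 1 to 1 | 80.0 % to 80.0 % |

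With ρx = 1 (a centre-level predictor) the factor becomes the design effect of step 3. So power rises with fewer centres only when the predictor clusters less than the outcome, stays the same when the two ICCs are equal, and falls when the predictor clusters more.

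**Step 5: the waves in the current design.** Centre-level predictor, 84 centres, method of step 3. At T1 (n = 476, m = 5.67) power is 94.5 %, 90.4 % and 81.0 % at ICC 0.05, 0.10 and 0.20. At T2 (476 × 0.8 ≈ 381 before new recruits, m = 4.54) it is 90.3 %, 85.9 % and 77.0 %.

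**The case against.** The strongest defence is that stress and physical activity, the main predictors, are measured on the child and the planned model is multilevel. For a predictor that clusters less by centre than the outcome, the variance factor does fall with fewer centres and power rises very slightly, as the remark says. This stands for that class of predictor (step 4). It rules out the stronger reading that 84 centres always cost power, or that power at N = 240 is below 80 % throughout. It does not rescue the remark, which carries no such restriction, in a study whose hypotheses include centre- and region-level predictors.

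A reader might also infer that the calculation ignored clustering, because 240 equals the unclustered size. The article does not support that inference. It names multilevel simulation software without showing its inputs, which an article may leave to the full protocol. A correct simulation with equal predictor and outcome ICCs would return the unclustered number. Slope-test formulas give 235 to 237, so the match with 240 also depends on the formula chosen. What remains is that no reserve for centre-level predictors is visible.

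Finally, a reader might take the remark as the article's answer to the shortfall in centres. It is an aside. The actual response is to recruit further children, and no target or analysis rests on the remark. T3 is moreover a worst case outside the current design, and at T1 and T2 power for centre-level predictors is well above 80 % at ICC 0.05 to 0.10. All of this stands and limits the severity.

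**Conclusion.** The remark is wrong as a general statement: at 240 children, 84 centres give a larger standard design effect than 96 for any positive ICC. For centre- and region-level predictors at T3 the cost is about 0.7 percentage points of power at an assumed ICC of 0.05 and 1.3 at 0.10. For child-level predictors the change is nil when they cluster as the outcome does, and a gain of about 0.03 to 0.11 points when they do not cluster at all (outcome ICC 0.05 and 0.10). The stated 80 % at N = 240 therefore fits child-level predictors. Centre- and region-level predictors fall somewhat short of it at T3.

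The direction follows from the article's own counts. The sizes rest on assumed ICCs, equal cluster sizes, the Fisher z approximation and r = 0.18. Severity: minor.

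**What to change.** In Study sample, delete the remark or reverse it: with the number of children fixed, fewer centres mean a slightly larger design effect and, for predictors that cluster by centre more than the outcome does, slightly lower power.

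Add one sentence saying that the 80 % at N = 240 refers to child-level predictors and that power for centre- and region-level predictors at T3 is somewhat lower. If a figure is given, label it as depending on an assumed ICC and on T3, and do not present it as achieved power.

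The cost is two sentences of text. Recruitment, the sample size target and the analysis stay as they are.
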